### The secondary hypothesis

Therapeutic DC results in fewer complications and a better quality of life compared with prophylactic DCThe risk of salvage craniectomy for post-operative refractory hypertension in primary craniotomy patients can be quantified by clinical features.

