### Statistical analysis

The analysis will be processed on the principle of intention. Patients who drop out or violate initial distribution will be considered as the worst outcome. Considering the probability of craniotomy patients treated by salvage DC, an as-treated analysis will also be implemented, as recommended in two-arm clinic trial [39]. Parametric data will be described by mean and standard deviation. Non-parametric data will be described by median and quartile. Categorical data will be presented using number and percentage.

The primary outcome of the study will be evaluated using the Pearson chi-square test with unadjusted risk ratio and 95 % confidence interval. Adjusted analysis of primary outcome will be assessed using logistic regression for pre-specified factors and any other covariates presenting significant difference between the two groups. The pre-specified subgroups include: age, GCS, pupillary response, mass lesion type and hypotension. Secondary outcome including assessment of quality of life, mortality at 6 and 12 months and incidence of complications will also be assessed using unadjusted analysis and adjusted regression. To investigate the risk factors of postoperative refractory hypertension (salvage DC), univariate and multivariate analysis will be used to identify potential variables of craniotomy patients.

Depending on the results of regression models, the receiver operating curves will be used to evaluate the discrimination. The Hosmer–Lemeshow test will process the goodness-of-fit of models [40]. A P value < 0.05 is considered statistically significant. All statistical analysis will be computed by SPSS software (version 19.0).

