### Sample size

The sample size calculation is on the basis of the variance of outcomes. The favorable outcome of DC in previous studies ranged from 30 % to 61 % [9, 15, 41–43]. Some results may not be applicable because they included patients with diffusion injury and used DC as a secondary therapy. When primary DC treated patients for mass lesions, the favorable outcome of prophylactic DC in 781 patients was 38 % [44–54]. In our centre using therapeutic DC, the favorable outcome of therapeutic DC was 54 % [30]. After including a safety margin of 10 % to account for patients who drop out, we calculate that a sample size of 336 (each arm 168) will be sufficient to reach a significance level of 5 % (two-side) and a power of 80 %. The sample size will be re-assessed and adjusted during interim analysis.

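### The salvage-craniectomy risk model, as described, would be judged by an upward-biased AUC from few events; name a short predictor list in advance and report an optimism-corrected AUC

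*Protocol article*

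**What the plan says.** The protocol article makes this a named aim. Under The secondary hypothesis it states that the "risk of salvage craniectomy for post-operative refractory hypertension in primary craniotomy patients can be quantified by clinical features".

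Statistical analysis gives the method: "univariate and multivariate analysis will be used to identify potential variables of craniotomy patients". It continues: "Depending on the results of regression models, the receiver operating curves will be used to evaluate the discrimination". For fit it adds: "The Hosmer–Lemeshow test will process the goodness-of-fit of models". The only significance level in the section is "A P value < 0.05 is considered statistically significant". No second data set is mentioned for assessing the model.

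Interventions determines who can enter this analysis. Every prophylactic-arm patient loses the flap at the primary operation. In the therapeutic arm the flap goes back only if the brain does not swell. Craniotomy patients therefore come from one arm only, and from part of it.

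**The concern.** Two features combine. The same patients would be used to choose the predictors, fit the model and measure its discrimination. The number of salvage events is also likely to be small relative to the number of variables collected. An AUC obtained this way is too high on average, and the bias grows as events become fewer.

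At stake is how the second secondary hypothesis is read. The Discussion names risk prediction as one of the two contested questions about DC. The Background says that the centre's previous result on initial intracranial pressure (ICP) needs prospective confirmation. An uncorrected AUC after data-driven selection cannot give that confirmation, because variables with no predictive value can produce a similar figure.

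**Working it through.** **The plan's own figure.** Sample size gives 336 patients, from favourable-outcome rates of 38% and 54%, two-sided 5%, power 80% and a 10% margin. The pooled formula without continuity correction is

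n = [1.960·√(2·0.46·0.54) + 0.842·√(0.38·0.62 + 0.54·0.46)]² / 0.16² = (1.381 + 0.586)² / 0.0256 ≈ 151.1, so 152 per arm.

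152 × 1.10 = 167.2, so 168 per arm and 336 in all. The figure reproduces. It is sized for the primary outcome; the article gives no salvage rate or event count for the risk model.

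**Patients available.** At most 168 (one arm). The Background cites a European retrospective series in which one third still needed DC after evacuation. Used as a proxy, this leaves 168 × 2/3 = 112. Assumed range: half to four fifths of the arm, 84 to 134.

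**Events.** The salvage rate is not stated. Assume 10–30%:
- low: 84 × 0.10 ≈ 8
- at 112 patients: 10% ≈ 11, 15% ≈ 17, 20% ≈ 22, 25% = 28
- high: 134 × 0.30 ≈ 40

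**Candidates.** Follow-up and data collection lists extracranial injury score, GCS, motor score, pupils, lesion type, volume, midline shift, time to operation, cause, blood gases, coagulation and platelets (12 items). It adds intra-operative readings at four time points. That is about 15; treating this collection list as the candidate list is an assumption. Events per candidate run from 8/15 ≈ 0.5 to 40/15 ≈ 2.7.

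**Chance that noise passes a screen.** With k independent noise variables and level α, P(at least one passes) = 1 − (1 − α)^k. At α = 0.05 this is 1 − 0.95^14 = 51% for 14 variables, 54% for 15 and 64% for 20.

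**Apparent AUC from noise.** Simulation: 14 independent noise predictors, univariate screen, logistic model on those that pass, AUC on the same patients. The true AUC is 0.50. A trial in which nothing passes counts as having no model.

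| Patients | Events | AUC ≥ 0.70, screen at 0.05 (all trials) | AUC ≥ 0.70, screen at 0.10 (all trials) |
|---|---|---|---|
| 112 | 11 | about 34% | about 50% |
| 112 | 17 | about 20% | about 34% |
| 112 | 22 | about 16% | about 24% |
| 112 | 28 | about 9% | about 19% |
| 134 | 40 | about 4% | – |

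At 0.05 with 112 patients a model appears in about half of trials. Among those, the mean apparent AUC is 0.66 (28 events) to 0.73 (11 events). The 0.10 column is for sensitivity only; that level is not in the article.

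**Hosmer–Lemeshow.** In a companion simulation with 15 or 20 noise predictors (half of them binary), 112 patients, 11–28 events and screens at 0.05 or 0.20, the test was non-significant in 89–99% of the noise models where it could be computed.

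**Effect of bootstrap correction.** In that simulation, a bootstrap repeating the selection lowered the mean AUC of the selected models from 0.66–0.80 to 0.54–0.64. Much of the optimism goes, but not all. On fresh data such models average 0.50.

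**The case against.** The strongest case against is that much of this is inferred. The article does not say that univariate results decide entry to the multivariate model. It does not give a candidate list, and it does not say how the ROC curve will be estimated. The swelling share and salvage rate are assumptions. A candidate list, entry rule and internal validation commonly sit in an analysis plan, which is not shown here, so their absence is not in itself an error. Pure, independent noise is also a worst case: the Background reports a possible signal for initial ICP, and some predictors are correlated. With plausible correlation at the 0.05 level, an AUC of at least 0.70 fell to 18% of trials at 17 events and 12% at 22.

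Most of that stands, and it limits the size of the point. A reader might infer that the plan is bound to report useful discrimination from noise, that good fit is guaranteed, or that the method itself would confirm the hypothesis. The documents do not support any of these. At the only stated level, about half of noise-only trials yield no model, and at every event count in the table most do not reach 0.70. Hosmer–Lemeshow passes most noise models, not all. No bone-flap decision rule is planned from this model.

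The stated method itself remains open to criticism. Using univariate and multivariate analysis to identify variables, then judging the result by ROC and Hosmer–Lemeshow, is a choice the article makes for a named hypothesis in a subset of one arm. Screening is the natural reading of that wording, and a better method is available at little cost.

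**Conclusion.** The concern holds as a bias in a secondary prognostic analysis. On the natural reading, the AUC of the salvage-DC model would be biased upward, and a non-significant Hosmer–Lemeshow test would give little protection. With 11–28 events in 112 patients, noise alone gives an AUC of at least 0.70 in roughly one trial in three down to one in eleven. With about 40 events the risk is small, around 4%.

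The size depends on four assumptions: screening at 0.05 with the AUC taken on the same patients, about 15 candidates, about one third of the therapeutic arm swelling, and a salvage rate of 10–30%. The direction of the bias does not depend on the exact event count. The planned ROC curve and Hosmer–Lemeshow test are conventional and need not be removed, and penalised fitting is optional.

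**What to change.** 1. Replace univariate screening with a short predictor list named before the data are seen and sized to the expected number of salvage events. Lead with initial ICP, the centre's own prior hypothesis in the Background, and add two or three of the minimisation factors under Randomization. At 11 events, four predictors still leave only 11/4 ≈ 2.8 events each, so the list should be shorter if events are few.
2. Beside the planned ROC curve and Hosmer–Lemeshow test, report a bootstrap optimism-corrected AUC and calibration slope. If any selection remains, repeat it within every bootstrap sample. The short list is needed as well, because the bootstrap alone left noise models at 0.54–0.64.
3. Label the model exploratory, and state the number of craniotomy patients and events with it.

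Ridge or Firth fitting is a reasonable option, not a requirement.

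Cost: a change of wording, a little more analysis work, possibly software beyond SPSS 19 for the bootstrap, and less flattering discrimination figures. No extra patients or data are needed.

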### Adverse events (AEs) and Serious adverse events (SAEs)

Both AEs and SAEs will be recorded in CRF. AE is defined as any unintended or unfavorable disease that occurs during the study. AEs include DC related complications, such as cortical herniation, hemorrhage evolution, infection, hydrocephalus and subdural hygroma. SAEs are defined as any of the following: death, life-threatening events, persistent vegetative state, requirement of hospitalization and prolonged hospitalization. Once the attending physicians realize SAE, it should be reported to the trial management team (TMT) and BMEC within 24 h. SAEs will be followed up until the issue is properly resolved.

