## Background

Severe traumatic brain injury (STBI) is a major cause of death in young adults in developed countries [1]. In China, due to increasing traffic accidents, head injury occurs above 1 per 1000 [2]. The mortality of STBI is between 30 % and 50 %. According to a report from the Asian Development Bank, the annual economic loss from traffic accidents is equivalent to 1 %–3 % of China’s gross national product [3]. Considering the per capita income and limited medical resources, rational and effective treatment of STBI is of important economic and social significance.

Most STBI patients with intracranial hypertension attribute to mass lesions, such as contusion and subdural haematoma (SDH) [4, 5]. Severe primary injury and exasperate condition necessitate emergent surgical intervention. The available type of operation is either craniotomy or decompressive craniectomy (DC).

Craniotomy is the most widely used surgical treatment for STBI. This operation keeps the skull intact but the risk of post-operative refractory hypertension remains; thus, requires a salvage surgery. DC is another broadly used operation for STBI rescue, which involves the removal of the frontal, parietal and temporal skull to expand fixed cranial cavity. Some studies indicated that DC could effectively alleviate refractory intracranial hypertension [6–10]. However, using DC to treat STBI has been controversial since the 1970s [11, 12]. The focus of debate resides in whether DC would be able to improve the prognosis of patients. Current guidelines only suggest performing set the role of DC as a ‘surgical choice’ [5, 13].

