### Follow-up and data collection

After randomization, patients will be assessed at 1 week and 1, 6 and 12 months. Patients who cannot be followed up at seven days will be assessed upon being discharged. For upfront exit patients, their surrogates should mark the previous data whether or not could be used in study. All patient information and imaging findings will be uploaded to a database using the case report form (CRF).

The initial data collection will be assessed at the emergency room by an attending physician. This collection will include baseline status, torso and/or extremities AIS, trauma severity (GCS, motor score and pupillary reaction), CT parameters (mass lesion type, volume of haematoma and midline-shift), time of injury-to-operation, cause of injury and initial laboratory features (arterial blood gas parameters, coagulation and platelet count).

The 1-week follow-up will include intra-operative brain swelling event, salvage craniectomy, laboratory features, early complications and ICP and CPP control. Intra-operative monitoring values will be recorded at the point of probe fixation, dura incision, dura suture and scalp closure. Post-operative ICP control will be recorded as daily ICP burden (number of hrs/d with ICP > 25 mmHg) and total ICP burden (number of days with ICP > 25 mmHg), as well as the same method recording daily and total CPP burden (CPP < 60 mmHg) [38].

At 1, 6 and 12 months follow-up, the independent blinded assessor will face-to-face evaluate intervention outcomes, quality of life, late complications and time of cranioplasty using standard questionnaire. The questionnaire includes the Extended Glasgow Outcome Score (GOSE), EQ-5D. If the discharged patients cannot attend scheduled follow-up, especially at time point of 6 or 12 months, the questionnaire will be sent to the documented permanent address. Only if these methods are invalid, the surrogate will be investigated to finish the questionnaire by telephone.

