### Outcomes

The Primary endpoint is a favorable outcome at 12 months after randomization as measured by GOSE (5–8). The core secondary endpoint is the quality of life indicated by EQ-5D. Further secondary endpoints include mortality and complications at corresponding time point, ICP and CPP control and incidence of salvage DC in craniotomy patients.

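### The between-arm complication comparison is described only through craniectomy-related examples, while salvage craniectomy is listed apart and confined to a subgroup that, as assigned, exists in one arm only

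*Protocol article*

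**What the plan says.** The secondary hypothesis of the protocol article is directional: therapeutic DC should give fewer complications than prophylactic DC. The Statistical analysis section makes this a comparison between groups: "mortality at 6 and 12 months and incidence of complications will also be assessed using unadjusted analysis and adjusted regression".

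The section on adverse events starts broadly, "AE is defined as any unintended or unfavorable disease that occurs during the study", and then gives its only examples: "AEs include DC related complications, such as cortical herniation, hemorrhage evolution, infection, hydrocephalus and subdural hygroma".

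The Background names the drawback of putting the flap back: "This operation keeps the skull intact but the risk of post-operative refractory hypertension remains; thus, requires a salvage surgery".

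Salvage DC appears in these places, each time beside complications and not among them:
- Outcomes: "Further secondary endpoints include mortality and complications at corresponding time point, ICP and CPP control and incidence of salvage DC in craniotomy patients".
- Follow-up and data collection: "The 1-week follow-up will include intra-operative brain swelling event, salvage craniectomy, laboratory features, early complications and ICP and CPP control".
- Abstract, Methods: salvage craniectomy in craniotomy patients is a separate item after complications and pressure control.
- Statistical analysis: "To investigate the risk factors of postoperative refractory hypertension (salvage DC), univariate and multivariate analysis will be used", a model fitted within craniotomy patients.

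**The concern.** Each strategy has its own typical harms. Leaving the flap off exposes patients to the craniectomy complications that the article lists. Putting it back leaves a risk of refractory intracranial hypertension and a second emergency operation. A fair comparison of complications has to let both kinds of harm register, by randomised arm.

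As worded, the first kind supplies every named example. The second sits in a separate endpoint whose denominator is craniotomy patients. Under Interventions the flap is always removed in the prophylactic arm, and in the therapeutic arm it is replaced only if the brain is not swollen. As assigned, craniotomy patients therefore come only from the therapeutic arm and are selected by an intra-operative finding. The salvage endpoint then has no comparator.

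At stake is the reading of a stated hypothesis. The trial could report fewer complications with therapeutic DC while repeat craniectomies in that arm appear only in a one-arm description.

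**Working it through.** **Figures in the plan.** The article gives no complication rate, no salvage rate and no share of the therapeutic arm expected to have the flap left off. The only usable input is 168 patients per arm (Sample size). That figure reproduces for the primary endpoint. With 54% versus 38%, two-sided 5% and 80% power, n = (1.96·√(2·0.46·0.54) + 0.8416·√(0.54·0.46 + 0.38·0.62))² / 0.16² ≈ 151.1, so 152 per arm; 152 × 1.10 = 167.2, so 168. It says nothing about complications. Everything below is illustration on assumed rates.

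**Does the wording place salvage DC inside or outside the count?**
- Pointing outside: the Abstract, Outcomes and Follow-up sections each list it separately, and Statistical analysis gives it its own within-subgroup model.
- Pointing inside: the adverse event definition is broad, the examples are open-ended, and many salvage episodes would probably meet the life-threatening or prolonged-hospitalisation criteria for a serious adverse event.
- No sentence settles it.

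**Upper bound on the shift.** Assume one third of the therapeutic arm has the flap left off at first surgery. Craniotomy patients = 168 × (1 − 1/3) = 112. If no salvage patient has any other complication, counting salvage adds (112 × rate) / 168 to the arm's complication rate. If other complications occur in 30% of the arm, independently of salvage, only 70% of salvage patients are newly counted.

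| Assumed salvage rate in craniotomy patients | Salvage patients | Added points, no overlap | Added points, independent 30% background |
|---|---|---|---|
| 5% | 5.6 | 3.3 | 2.3 |
| 10% | 11.2 | 6.7 | 4.7 |
| 20% | 22.4 | 13.3 | 9.3 |

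If every salvage patient already has a counted complication, the shift is zero.

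**Effect on the arm difference.** Let p_C and p_T be the assumed complication rates without salvage, and s the salvage rate in the whole therapeutic arm. With independence, the therapeutic rate including salvage is p_T + s(1 − p_T). Salvage DC cannot occur in the prophylactic arm as assigned. Other unplanned reoperations in either arm are set to zero here.

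| p_C versus p_T | Benefit without salvage | s = 5% | s = 10% | s = 15% |
|---|---|---|---|---|
| 40% vs 30% | 10 points | 6.5 | 3.0 | −0.5 |
| 40% vs 25% | 15 points | 11.3 | 7.5 | 3.8 |
| 30% vs 20% | 10 points | 6.0 | 2.0 | −2.0 |

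For example, 0.30 + 0.15 × 0.70 = 0.405, and 40% − 40.5% = −0.5 points. On these assumptions, whether salvage counts can shrink the benefit substantially and, at the upper end, reverse its sign.

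**The case against.** The strongest reply is that the article never says the complication endpoint equals its list of examples, nor that salvage DC is left out of it. Separate listing is not exclusion: mortality is also listed apart from complications, yet death is a serious adverse event. A full protocol and case report form lie behind the article and may define the components. This stands, and it rules out a stronger reading that a reader might draw, namely that the hypothesis is tested on a craniectomy-only list and is favoured by construction.

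Four further points limit the concern:
- Infection, haemorrhage evolution and hydrocephalus are not shown to be confined to flap removal. The therapeutic arm also contains patients whose flap is left off, at first surgery or after salvage, and their listed complications count there.
- Intracranial hypertension is not lost. Pressure is monitored in both arms, and its control is a secondary endpoint; in "ICP and CPP control and incidence of salvage DC in craniotomy patients" the restriction to craniotomy patients most naturally attaches to salvage DC alone.
- The consequences of salvage surgery enter the 12-month functional outcome, mortality and quality of life by intention to treat.
- Salvage DC cannot happen to a patient whose flap is already off, so adding it alone would bring in a component that only one arm can incur.

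The reply does not dispose of the point. This is more than detail left to another document. The article sets a directional hypothesis, draws all its examples from one strategy's harms, and gives the other strategy's characteristic harm a denominator with no counterpart. Followed as written, salvage surgery has no between-arm comparison.

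**Conclusion.** The concern holds in a limited form. The text does not fix whether salvage DC counts as a complication, its wording points towards not counting it, and the endpoint that does hold salvage DC is a post-randomisation, one-arm subgroup. A complication count built on that wording would tend to favour the therapeutic arm.

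The documents do not support saying that the comparison is biased by construction or that a second craniectomy is certain to go uncounted. The size is unknown. The 3.3 to 13.3 points are upper bounds that rest on an assumed one-third flap-off share, assumed salvage rates of 5% to 20% and no overlap with other complications; with an independent 30% background they fall to about 2.3 to 9.3. The primary endpoint and the sample size are not affected. The change is worth making because it removes a one-sided reading of a stated hypothesis at little cost.

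**What to change.** In Outcomes and Statistical analysis:
- Compare complications by randomised arm in all randomised patients, using one common event set applied identically to both arms.
- Report the comparison twice: without, and with, salvage DC or any other unplanned cranial reoperation. Including any unplanned reoperation lets both arms contribute events.
- Keep salvage incidence in craniotomy patients, and its risk-factor model, as description only.
- Keep pressure control as its own between-arm endpoint. Putting malignant hypertension into the same composite as the salvage surgery it triggers would join two linked events.

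The cost is mainly wording. Salvage craniectomy and early and late complications are already collected. The article does not name other unplanned reoperations as a data item, so the case report form may need one field. The downside is that the expected advantage of therapeutic DC on complications may become smaller.
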